#### ​Indication for prescribing

OACs are prescribed for many different indications, but only those prescribed for stroke prevention in AF will be included in this study. Patients will be excluded from the study if

They had a hip fracture or hip replacement in the 6 weeks prior to the OAC index date and only one prescription for an OAC.They had a venous thromboembolism in the 6 months prior to the OAC index date.

#### 
*​*DOAC prescription duration

The index date will be defined as the date the first prescription was issued. The expected end date will be calculated by dividing the number of tablets prescribed by the licensed number of doses per day (ie, two doses per day for dabigatran and apixaban and one dose per day for rivaroxaban and edoxaban). Where the quantity of tablets prescribed is not specified, the expected duration will be imputed from other prescriptions issued for the same product for that patient or overall for that product if patient-specific information is not available.

Patients will be classified as being continuously exposed until there is a gap of >60 days between the expected end of one prescription and the start of the next. Where there is a gap of ≤60 days between the expected end of one prescription and the start of another for the same DOAC (regardless of whether the strength prescribed changes), the gap will be filled and defined as continuous exposure. Where a subsequent prescription for the same product is issued before the expected end of the previous prescription, the prescriptions will be concatenated and the extra days will be added to the expected end date of the second prescription. A maximum of 60 additional days will be allowed per patient.

A DOAC will be defined as discontinued 60 days from the expected end date of the last prescription issued for that product.

#### 
*​*Warfarin prescription duration

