Warfarin does not have a fixed dosing schedule; the dose is amended based on the results of a blood test, the international normalised ratio (INR). In the UK, patients are issued with different strength tablets (0.5, 1.0, 3.0 and 5.0 mg) and are advised, following each INR test, what dose they need to take and what strength of tablets to use. Dosing information for warfarin is not recorded in the CPRD; however, the strength and quantity of warfarin tablets issued by the general practice are recorded. Read codes for warfarin monitoring and results of INR tests are also recorded by some general practices, but this is not recorded consistently.

The index date will be defined as either the date of the first prescription issued or from the date of the first INR test result above 2 if this occurs before the first issue of a prescription. Patients may be exposed to warfarin before the first prescription issued by their GP if treatment is started in the hospital. CPRD data do not include hospital prescribing; hence, INR test results of ≥2 will be used as a surrogate marker of exposure.

The expected end date for warfarin prescriptions will be estimated using the median time between all previous prescriptions issued to the same patient. For example, if four prescriptions had been issued for 28×1 mg tablets and the gaps between the prescription issue dates were 15, 35 and 42 days, we would define the final prescription for 28 tablets as lasting 35 days, so the expected end date of the last prescription would be 35 days from the issue date. Where multiple strengths are issued for a patient, the median will be calculated for each strength and the expected end date will be the latest of these dates.

If only one prescription has been issued, the expected end date will be assumed to be equal to the median warfarin prescription gap for the cohort.

A patient will be assumed to have discontinued warfarin treatment if there is a period ≥2 times their median prescription gap. If an INR test result of ≥2 is recorded in the discontinuation period (expected end date of the last prescription to the date equal to twice their median prescription gap), then INR tests will be used as a surrogate marker for warfarin prescribing and the end date will be defined as 1 week following the final INR test result of ≥2.

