#### ​Objective 4: to describe persistence with DOACs compared with warfarin

Duration of prescribing of DOACs will be compared with warfarin using Cox proportional hazards, stratified by DOAC and adjusted for age and other important covariates identified in objective 3. All incident OAC users will be included. Time on OAC will be calculated as the difference between the discontinuation date of the OAC and the index date, as defined previously. Patients will be censored at the outcome (discontinuation of OAC therapy), on the date they stop contributing research standard data or the date of death.

All analyses will be conducted in STATA V.15.^24^ All values will be reported with 95% CIs.

#### 
*​*Missing data

There is likely to be a substantial amount of missing data for weight, BMI, smoking status and alcohol consumption as these variables may not be regularly updated by GP practices. We will use logistic regression to ascertain whether other variables (age, sex or comorbidities) predict whether these data are missing. If these variables do not predict the missing data, then we will assume that the data are missing at random. The proportion of missing data for these variables will be presented. If the data are missing at random, we will impute the missing values using multiple imputation and conduct a sensitivity analysis to investigate the effect of the missing data on the results of the analyses. However, previous studies suggest it may only be appropriate to impute weight and BMI.^25 26^

## 
*​*Patient and public involvement

Patients and the public were not involved in the production of this protocol or in the design of the study.

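### Objective 4 puts DOACs and warfarin in one Cox model, but discontinuation is defined with a different grace period for each class, so the hazard ratio partly reflects the definitions

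*Protocol article*

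**What the plan says.** All from the protocol article.

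- **Comparison (Statistical analysis, Objective 4).** "Duration of prescribing of DOACs will be compared with warfarin using Cox proportional hazards". The time variable takes over the class-specific definitions: "Time on OAC will be calculated as the difference between the discontinuation date of the OAC and the index date, as defined previously". Only incident users enter.
- **DOAC (DOAC prescription duration).** Supply is the tablet count divided by licensed daily doses. The gap rule reads: "Patients will be classified as being continuously exposed until there is a gap of >60 days between the expected end of one prescription"; the gap is measured up to the following issue. The stop date is then set by a fixed allowance: "A DOAC will be defined as discontinued 60 days from the expected end date of the last prescription issued for that product". Early refills carry forward: "A maximum of 60 additional days will be allowed per patient". The clock starts at the first prescription.
- **Warfarin (Warfarin prescription duration).** Supply is the patient's own median gap between issues. "A patient will be assumed to have discontinued warfarin treatment if there is a period ≥2 times their median prescription gap". An INR of at least 2 in the discontinuation window moves the end date to one week after the last such result. With several tablet strengths, the latest discontinuation date counts. The clock starts at the first prescription, or "from the date of the first INR test result above 2 if this occurs before the first issue of a prescription".
- **Both classes (Restarting index OAC after discontinuation).** Anyone classed as stopped who later resumes the index drug is reviewed individually, to see whether the record offers another explanation, such as a hospital stay.

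The strengths and limitations box and the Discussion say that warfarin duration is estimated and hard to define. Neither says that the two compared groups have different event rules.

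**The concern.** Discontinuation is the event in Objective 4. If one class must go longer without a prescription before it counts as stopped, the hazard ratio mixes patient behaviour with the measuring rule. The missing warfarin dose justifies estimating supply differently. It does not justify a different grace period: once the median gap has produced an expected end date, any grace can be added to it, including the 60 days used for DOACs.

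The start of the clock differs too. A warfarin patient whose time starts at an INR before the first prescription gains days in which no event can occur, because a prescription must follow. DOAC patients have no such days.

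**Working it through.** **1. The plan's own example.** Gaps of 15, 35 and 42 days: median = 35, as the article states.

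**2. Grace and threshold.** For a median gap or supply of m days:
- warfarin: threshold 2m from issue, so grace = 2m − m = m;
- DOAC: threshold m + 60 from issue, so grace = 60;
- equal when 2m = m + 60, that is m = 60.

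| m (days) | Warfarin: days from last issue (grace) | DOAC, same supply: days from last issue (grace) |
|---|---|---|
| 28 | 56 (28) | 88 (60) |
| 35 (article's example) | 70 (35) | 95 (60) |
| 56 | 112 (56) | 116 (60) |
| 60 | 120 (60) | 120 (60) |
| 84 | 168 (84) | 144 (60) |

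**3. Effect on the hazard ratio.** The article gives no issue intervals, refill variability or stopping rates, so every input here is an assumption. The simulation had 6,000 patients per class and a true hazard ratio of 1. True stopping was 0.35 per year and censoring was uniform from 0.5 to 5 years. Refill gaps were log-normal with mean equal to the DOAC supply, and both classes had the same issue pattern. DOAC carry-over was included. The warfarin stop date was taken as last issue + 2 × median. INR-based end dates and multiple strengths were not modelled. Hazard ratios are DOAC versus warfarin:

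| Interval, CV of gaps | Written rules, no restart reinstated (whole-record median) | Same, running median of earlier gaps | Every restart reinstated | One 60-day rule for both |
|---|---|---|---|---|
| 28 d, 0.2 | 0.92 | 0.91 | 0.98 | 1.00 |
| 28 d, 0.4 | 0.39 | 0.33 | 0.92 | 1.00 |
| 28 d, 0.6 | 0.20 | 0.18 | 0.95 | 1.02 |
| 56 d, 0.2 | 0.99 | 0.96 | 1.00 | 0.98 |
| 56 d, 0.4 | 0.73 | 0.58 | 1.00 | 0.98 |
| 56 d, 0.6 | 0.57 | 0.47 | 1.00 | 1.02 |
| 84 d, 0.2 | 1.07 | 1.06 | 1.04 | 0.99 |
| 84 d, 0.4 | 1.14 | 0.93 | 1.02 | 0.97 |
| 84 d, 0.6 | 0.91 | 0.72 | 0.99 | 1.01 |

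The last column isolates the rule mismatch as the cause. Reinstating every restart still leaves the stop date itself set by different rules: at 28-day supply, 88 − 56 = 32 days later for a DOAC.

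**4. Start clock alone.** Common stop rule, 28-day issues, CV 0.2, all restarts reinstated, true stopping 0.35 or 0.7 per year, standard error of the log hazard ratio 0.021 to 0.025:
- half of warfarin patients starting 28 days early: 1.00 and 1.02;
- half starting 90 days early: 1.07 and 1.12;
- all starting 28 days early: 1.07 and 1.06.

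**5. Loose ends in the same section.** The text does not say outright whether a warfarin stop is dated at the expected end or at twice the median; Figure 1, which is not shown, may settle this. If it is twice the median, an INR of 2 or more on day 36 in the 35-day example ends exposure on day 36 + 7 = 43, against day 70 with no INR. If the median runs over earlier gaps only, the example patient is already classed as stopped at the second gap, since 35 ≥ 2 × 15 = 30. The start trigger is an INR above 2 in one sentence and at least 2 shortly after.

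**The case against.** **Restart review.** A persistent patient with a late refill goes on to receive the same drug, so every false stop of that kind reaches the individual review. If the review reinstates them all, most of the distortion disappears (0.92 to 1.04). This stands as a limit on size. It is not a cure: the review looks for a recorded reason, a late refill from leftover tablets need not leave one, and no default is given when none is found.

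**A larger bias.** A reader might work out false stops for fully persistent patients (log-normal gaps, sigma 0.35, true stopping 20% a year) and arrive at hazard ratios of 0.45, 0.91 and 1.50 for 28-, 56- and 84-day supply. The documents do not support those as the expected bias. They leave out the restart review, the DOAC carry-over and the latest-strength rule, and they rest on one chosen sigma. Nor does the fact that about half of gaps exceed the median show that twice the median is easily crossed. In that model the chance per gap is 2.4% at sigma 0.35, 0.28% at 0.25 and 0.03% at 0.20.

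**Start clock.** A reader might infer that the INR lead has no limit. Incident users need a year free of OAC before study entry, so an INR treated as exposure in that year would naturally make the patient prevalent. Lead time within the cohort has no stated limit, but the effect is small unless leads are long or common.

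**Forced asymmetry, disclosed.** Warfarin dosing is not in the database, and the article admits the difficulty. That covers the estimate of supply, not the unequal grace. INR bridging helps only in part, because the article says INRs are inconsistently recorded, and it applies to warfarin alone.

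**Conclusion.** The point holds in a moderate form. The article fixes two different discontinuation rules and feeds both into one hazard ratio, so this is not a detail left to an analysis plan. With equal true persistence the estimate can move away from 1. Short issue intervals make warfarin look less persistent, intervals above 60 days can do the reverse, and an INR start favours warfarin.

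The size is uncertain because it depends on issue intervals and variability that the article does not give. On the assumptions above and with the whole-record median, it runs from about 0.9 to 1.1 with regular issuing to 0.2 to 0.4 with irregular 28-day issuing. The extreme values assume that no restart is reinstated and are therefore upper bounds on the distortion; full reinstatement gives 0.92 to 1.04. The start clock is secondary.

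A reader might conclude that the Objective 4 result cannot be interpreted at all. The documents do not support that: the restart review can remove much of the effect, and Objective 4 is one of four objectives, framed as descriptive. Should-fix.

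**What to change.** For Objective 4:

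1. Apply one grace period to both classes: 60 days after expected end, with warfarin expected end = issue date + the patient's median gap. Use one stop-date convention. Make this the main analysis, or at least a pre-specified sensitivity analysis beside the current rule.
2. Start time at the first GP prescription for both classes, or bring INR-started patients in by delayed entry at that prescription.
3. Vary the common grace period, for example 30 and 90 days.
4. In the section on restarting the index OAC, state how a restarted patient is classified when the record shows no reason for the gap, and apply that default identically to both classes.
5. While editing, say whether the median uses the whole record or only earlier gaps, and make the INR threshold consistent.

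The cost is wording, re-parameterised code and a few extra runs on data already in hand. Some misclassification of warfarin supply will remain, because the daily dose is not recorded.

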**Figure 1 F1:**
[figure not shown]
Illustration of warfarin mapping for a single patient and one strength of warfarin tablet. Rx, prescription.

#### 
*​*Restarting index OAC after discontinuation

There could be instances where OAC therapy is classed as discontinued when in fact the OAC has been continued but not issued by a GP if the patient is hospitalised. In instances where patients are classified as discontinuing OAC therapy but have then been ‘restarted’ on their index OAC, they will be reviewed individually to ascertain whether the OAC therapy had truly been discontinued or whether their records indicate another reason for the gap in prescribing, for example, a record indicating an admission to hospital.

#### ​OAC switching

The first OAC prescribed during the study (for incident users) or on entry to the study (for prevalent users) will be defined as the index OAC. If ≥1 prescription for an alternative OAC is prescribed during the study period, the patient will be designated as having switched. Switches can be from

Warfarin to DOAC.DOAC to warfarin.DOAC to alternative DOAC.

Patients will be assumed to have stopped the index OAC on the date the alternative OAC is issued if this is prior to the expected end date of the index OAC. Where the alternative OAC is prescribed after the expected end date of the index OAC, the time to switch will be described.

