### Statistical analysis

#### Objective 1: to describe changes in the point prevalence and incidence of OAC prescribing by year prior to the introduction of DOACs (2003–2007), between the introduction of DOACs and the time they were recommended by NICE for stroke prevention in AF (2008–2012), and following NICE recommendation (2013–2017).

Only patients prescribed an OAC will contribute data to the incidence and prevalence calculations. For incidence, patients may only contribute to either the warfarin or the DOAC group once as they will be censored at the time they are prescribed an OAC. The point prevalence will be calculated at the midpoint of each year so will take account of switching. For prevalence, a patient could contribute to the warfarin group for some years, and the DOAC group for other years. Prescription mapping will be used to calculate the number of people with an OAC prescription that includes that time point as the numerator and the total number of people in the cohort at that time point as the denominator.

The incidence of OAC prescribing will be calculated overall and for each specific OAC. Everyone in the cohort will be considered ‘at risk’ until the time they receive their first OAC prescription. Incidence will be calculated using the number of incident OAC users as the numerator and person-time at risk for non-exposed persons as the denominator. For the person-time at risk calculation, the denominator will be truncated at the date of their first OAC prescription. Incidence will be stratified by age (75–84 and 85+) and sex.

Figure 2 illustrates how patients may contribute to the incidence and prevalence calculations throughout the study.

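### A switch made after the expected end date does not close the index DOAC, so up to 59 days on the new drug are credited to the old one

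*Protocol article*

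**What the plan says.** Three sets of rules in the protocol article meet here.

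- **OAC switching.** "Patients will be assumed to have stopped the index OAC on the date the alternative OAC is issued if this is prior to the expected" (the date meant is the index drug's expected end). The next sentence covers the later case: "Where the alternative OAC is prescribed after the expected end date of the index OAC, the time to switch will be described". It sets no stop date for the index drug.
- **DOAC prescription duration.** "Patients will be classified as being continuously exposed until there is a gap of >60 days between the expected end of one prescription" (the gap closes when another prescription begins). The stop date is then fixed: "A DOAC will be defined as discontinued 60 days from the expected end date of the last prescription issued for that product". No exception is made for a switch. Short gaps are filled only within one product: "Where there is a gap of ≤60 days between the expected end of one prescription and the start of another for the same DOAC".
- **Warfarin prescription duration.** "A patient will be assumed to have discontinued warfarin treatment if there is a period ≥2 times their median prescription gap". The discontinuation period is described as "expected end date of the last prescription to the date equal to twice their median prescription gap". An INR of 2 or more in that period moves the end date to one week after the last such result. With several tablet strengths, the patient is unexposed from the latest of the strength-specific discontinuation dates.

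Two analyses use the mapped dates. Objective 4 takes time on OAC as discontinuation date minus index date. For Objective 1, "Prescription mapping will be used to calculate the number of people with an OAC prescription that includes that time point as the numerator"; the section adds that mid-year prevalence takes account of switching, with a patient in the warfarin group in some years and the DOAC group in others.

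**The concern.** The mapping rules carry exposure past the expected end date by a grace period, but the switching rule cuts the index drug off only before that date. Between the expected end and the end of the grace period, no sentence closes the old drug when a new one is issued. For a DOAC, the 60-day rule then supplies the stop date.

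Most at stake is Objective 4. A late switcher is given index-drug time that the records show was spent on another anticoagulant. The amount depends on which side of an estimated date the switch happened to fall. It also depends on the drug, since the grace period is 60 days for a DOAC and patient-specific for warfarin. The excess therefore need not cancel in the comparison of DOACs with warfarin. A smaller stake is drug-specific prevalence, where one patient could appear in two numerators at the same mid-year date.

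**Working it through.** The article gives no figure for overlap, so there is none to reproduce. Its one related figure, the warfarin example with gaps of 15, 35 and 42 days, does reproduce: the median is 35 days.

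**Inputs.** Day 0 is the expected end date of the index OAC, and s is the day the alternative is issued.
- Stop = s if s < 0 (OAC switching).
- Stop = +60 if s > 0, index DOAC (DOAC prescription duration).
- Stop = +35 if s > 0, index warfarin in the 35-day example. This assumes that the stop date is twice the median gap: 70 days from issue, less the 35 days to the expected end.
- Overlap = stop − s, where positive and s lies within the grace period.

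| Switch day s | DOAC stop | DOAC overlap | Warfarin stop | Warfarin overlap |
|---|---|---|---|---|
| −1 | −1 | 0 | −1 | 0 |
| +1 | +60 | 59 | +35 | 34 |
| +20 | +60 | 40 | +35 | 15 |
| +30 | +60 | 30 | +35 | 5 |
| +59 | +60 | 1 | past grace | – |

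**Jump in stop date.** Moving the switch by two days, from −1 to +1, moves the DOAC stop date by 60 − (−1) = 61 days. In the warfarin example it moves by 35 − (−1) = 36 days.

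**Day 0.** A switch exactly on the expected end date is neither before nor after it, so neither sentence of the switching section covers it.

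**Mid-year prevalence.** This part assumes that grace days count as mapped exposure and that switch days are uniform over the grace period.
- DOAC: the mean overlap is (59 + 58 + … + 0)/60 = 1770/60 = 29.5 days. A given mid-year date falls inside it for 29.5/365 = 8% of late switchers, and at most 59/365 = 16%.
- Warfarin example: the mean overlap is (34 + 33 + … + 0)/35 = 595/35 = 17 days, giving 17/365 = 5%, and at most 34/365 = 9%.

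These are shares of patients who switch within the grace period in that year, not shares of all users of the drug.

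**With the index drug capped at the switch.** Stop = s for every s in the grace period, so overlap is 0. The DOAC stop date moves earlier by 60 − s days (59 to 1), and going from s = −1 to s = +1 moves it by 2 days instead of 61.

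**The case against.** The strongest defence is that the article never says a late switcher is on two drugs. Describing the time to switch can be read as measuring a gap that opens at the expected end, with the index drug already over. Gap filling is confined to the same DOAC, and Objective 1 says that prevalence allows for switching. The article also condenses a fuller approved protocol, where precedence between drugs could be settled.

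Part of this stands. A reader might infer that the plan deliberately adopts dual exposure. It does not; the overlap is a consequence of the only stop date written. But the gap reading conflicts with the DOAC rule, which puts discontinuation 60 days after the expected end without exception, and with Objective 4, which uses that date. Two programmers could reach different stop dates from the same text. The stated rules themselves give the wrong end, so this is more than omitted detail.

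Three stronger inferences are tempting and are not supported:

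- **That index warfarin is affected to a known extent.** The text gives a criterion for discontinuation but does not clearly say that the stop date is twice the median gap. Figure 1 is not available here, and INR results can shift the date.
- **That about half of warfarin switches fall in the window, because the expected end is a median.** This assumes that switches happen when a renewal would have been due, which the article does not say. With several strengths, the expected end is also the latest of several dates.
- **That the warfarin trend after DOAC introduction is overstated.** This needs the grace period to count as prescription time in the prevalence numerator, which is not stated. It concerns drug-specific counts only, and the number of late switchers is unknown.

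Ending the index drug at its expected end would also remove the overlap. It would, however, give late switchers no grace time at all, while patients who simply stop a DOAC receive 60 days.

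**Conclusion.** The point holds firmly for index DOACs and with less certainty for warfarin. Read literally, the article credits a DOAC patient who switches 1 to 59 days after the expected end with 59 to 1 days on the old drug after the new one was issued. The stop date has a 61-day discontinuity at an estimated date. For warfarin the corresponding maximum is 34 days in the article's 35-day example, on condition that the stop date is twice the median gap and no INR result moves it.

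The main effect is on persistence in Objective 4. Its direction in the DOAC–warfarin comparison cannot be stated, because it depends on how many late switchers each group has. For drug-specific mid-year prevalence, the chance of double counting is about 8% of late DOAC switchers (maximum 16%) and about 5% of late warfarin switchers (maximum 9%), under the two assumptions stated in the working. Overall OAC prevalence counts each person once, and incidence is censored at the first OAC, so neither is affected. The number of patients concerned cannot be derived from the article. The correction is worth making before the exposure mapping is programmed.

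**What to change.** In the section on OAC switching, state that the index OAC ends at the earlier of its mapped discontinuation date and the date on which an alternative OAC is issued. This also settles the switch that falls exactly on the expected end date. Add that INR results recorded after a DOAC has been issued do not extend warfarin exposure.

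Keep the planned description of time from expected end to switch, for every switch after the expected end date. The change concerns the stop date only and should not narrow that description.

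The cost is one further line of mapping code and slightly shorter index-drug durations for late switchers. No additional data are needed.
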